### ShockTalk App: How It Works

ShockTalk (Figure 2) is a mobile app that uses Facebook Messenger as its entry point for clients. When a client first connects, they are greeted by ShockTalk’s artificial intelligence (AI) assistant, which guides them through the initial process. The AI collects basic contact information, helps synchronize important dates directly to the client’s calendar, and offers an option to schedule a 15-minute intake session with a licensed therapist from ShockTalk’s vetted health care provider directory.

Before the intake appointment, the AI sends reminder messages to help clients prepare. During the intake, the therapist and client discuss needs, goals, and preferences. Together, they decide whether the therapist is a good fit for ongoing care. If so, they begin a therapeutic relationship within the platform. If not, the therapist helps connect the client to other appropriate services or health care providers.

**Figure 2 figure2:**
[figure not shown]
Preview of the ShockTalk tele–mental health linkage-to-care app.

### Objective

The ShockTalk team has partnered with a researcher affiliated with the Columbia University School of Social Work to evaluate the pilot and feasibility of this app, which will involve interviews with 10 Indigenous mental health treatment seekers in Lenapehoking and 3 practitioners. The aims of this research are as follows: (1) assess changes in client attitudes related to tele–mental health treatment value and trust in ShockTalk technology; (2) assess the accessibility, experience, and value of ShockTalk for practitioners and clients interested in providing or receiving culturally responsive mental health treatment; and (3) estimate the potential benefit of the culturally responsive mental health treatment facilitated by ShockTalk. The ultimate evaluation of this pilot program will assess the prospective benefits of tele–mental health care linkage for Indigenous individuals living in urban settings.

## Methods

### Overview

To test the feasibility of ShockTalk among Indigenous clients, we will conduct a small pilot study with 10 Indigenous therapy-seeking clients and 3 Indigenous mental health practitioners in Lenapehoking. This study was designed as a preliminary feasibility pilot to inform a larger trial and, therefore, was not prospectively registered.

After informed consent and baseline assessment, clients will be randomly allocated 1:1 to immediate access to ShockTalk (treatment) or to a 3-month waitlist control (5 clients per arm). The allocation list will be generated by a study team member not involved in enrollment and uploaded to a centralized randomization module, which will reveal the assignment only after baseline data entry. Allocation events will be logged. In the absence of a centralized system, sequentially numbered, sealed opaque envelopes prepared from the same allocation list will be used.

All participants will complete baseline surveys and a 3-month follow-up survey (3 months postrandomization). Waitlist participants will be offered access to the linkage-to-care intervention 3 months after their initial baseline survey is completed. Qualitative data collection at 3 months from baseline will include 1-hour semistructured interviews (Multimedia Appendix 1) with a purposive subsample of 5 clients (selected to reflect a range of engagement and experiences across arms) and a single focus group with participating practitioners. Finally, a preliminary cost analysis will be conducted using data from both arms to assess the feasibility of cost data collection and to generate exploratory cost estimates across varying levels of engagement. Analyses will be descriptive and feasibility-focused (ie, recruitment, retention, acceptability, and data completeness); inferential effectiveness claims will not be made given the pilot sample size.

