### Measures

#### Quantitative Measures

The first survey instrument will examine changes in attitudes related to tele–mental health treatment value for clients before and after treatment facilitated by ShockTalk. One month before treatment and 3 months after treatment, clients will be given the Attitudes Toward Seeking Professional Psychological Help-Short Form survey [24]. This survey measures participants’ openness to seeking professional help for emotional problems and the value and need for seeking professional help. Clients are asked whether they disagree, partly disagree, partly agree, or agree with an item, including questions such as, “The idea of talking about problems with a psychologist strikes me as a poor way to get rid of emotional conflicts” and “A person with an emotional problem is not likely to solve it alone; he or she is likely to solve it with professional help.” Their attitudes toward seeking professional help are scored based on the sum of all responses. The short version of the scale demonstrates internal consistency ranging between 0.82 and 0.84, and high test-retest reliability (a=0.80) [24]. Once the presurveys and postsurveys are collected, the study team will examine the differences in openness to treatment before and after ShockTalk*.* A positive difference between the pretreatment and posttreatment Attitudes Toward Seeking Professional Psychological Help-Short Form score will indicate an increase in client valuation of mental health care treatment. *t* tests (1-tailed) will be used to evaluate whether the differences are statistically significant.

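### Waitlist access is timed from the baseline survey but the follow-up survey from the later randomisation, so access can open before the control measurement is due

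*Protocol article*

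**What the plan says.** The Overview under Methods fixes the sequence of events: "After informed consent and baseline assessment, clients will be randomly allocated 1:1 to immediate access to ShockTalk (treatment) or to a 3-month waitlist control". The randomisation module confirms the order, since it is one "which will reveal the assignment only after baseline data entry". Randomisation therefore cannot come before the baseline survey.

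The same section then sets three month-3 events:

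- Follow-up survey, counted from randomisation: "All participants will complete baseline surveys and a 3-month follow-up survey (3 months postrandomization").
- Waitlist access, counted from the baseline survey: "Waitlist participants will be offered access to the linkage-to-care intervention 3 months after their initial baseline survey is completed".
- Client interviews and practitioner focus group, also counted from baseline: "Qualitative data collection at 3 months from baseline".

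Quantitative Measures counts from treatment instead: "One month before treatment and 3 months after treatment, clients will be given the Attitudes Toward Seeking Professional Psychological Help-Short Form survey".

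The article states no interval between baseline and randomisation, and no sentence says that a waitlist client completes the follow-up survey before being offered access.

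**The concern.** The month-3 survey of the waitlist arm is the only concurrent follow-up measurement meant to be taken without ShockTalk. If access opens first, some controls may answer it after contact with the app.

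That contact need not include therapy. The section on how the app works says that an AI assistant greets a client at first connection and can book a 15-minute intake. The trust items (PATAT) ask about ShockTalk itself, for example its privacy and its safekeeping of personal information, so a brief encounter could alter the answers. An intake could also alter views on the value of professional help, which the attitudes scale (ATSPPH-SF) measures.

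What is at stake is how cleanly a descriptive contrast can be read, not the validity of a powered test. It still matters, because Limitations and Future Research says the findings will feed the sample size of a later randomised trial.

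**Working it through.** **Inputs.** B is the date of the baseline survey and R the date of randomisation. From the Overview, R is on or after B. Write g = R − B, so g ≥ 0. The article gives no figure for g, so every value above 0 below is an assumption. Three months is taken as 91 days.

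**Dates under the Overview as written.**

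- Waitlist access offered: B + 3 months.
- Follow-up survey due: R + 3 months = B + g + 3 months.
- Lead of access over survey: (B + g + 3 months) − (B + 3 months) = g.

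Because g cannot be negative, access never opens after the survey's due date.

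**Values of g.**

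| Assumed g | Access opens before survey is due by | Share of 91 days |
|---|---|---|
| 0 days (same-day allocation) | 0 days; same date, order not stated | 0% |
| 7 days | 7 days | 7/91 = 8% |
| 14 days | 14 days | 14/91 = 15% |
| 30 days | 30 days | 30/91 = 33% |

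The last row applies if the survey that Quantitative Measures places one month before treatment is the baseline survey, and immediate access starts at randomisation. The unexposed period counted from randomisation is then about 3 − 1 = 2 months.

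**The treatment-based schedule.** If treatment for a waitlist client means ShockTalk access, it starts no earlier than B + 3 months. The post survey then falls no earlier than B + 3 + 3 = B + 6 months, after the client has had access. On that reading it is not a control measurement, so Quantitative Measures does not resolve the mismatch in the Overview.

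**After the fix.** If the survey window closes before B + 3 months, the survey is due before access for any g, and the scheduled lead of access over survey is 0.

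**Weight of one client.** The plan is "3-month waitlist control (5 clients per arm"), so one affected control is 1/5 = 20% of the planned arm. Results reports 4 clients enrolled in total and does not give the split by arm.

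**The case against.** The best reply is that the mismatch may have no practical effect. Allocation can follow baseline data entry on the same day, making g zero. Access is only offered: the client must still open Messenger, then book and attend an intake. The Overview calls the analyses descriptive and rules out inferential effectiveness claims, and no analysis section names a test of immediate access against waitlist. All of this stands. It limits the size and weight of the point, but a shared date with no stated order would remain even at g = 0.

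A second reply is that survey windows and reminders belong in a full protocol. That is right for windows as such. Here, though, the article states both time origins, and they conflict.

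Two stronger readings are tempting and should be resisted:

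- **Overlap of several weeks.** A reader might add late survey return to g. Late return would occur with a single origin too, and the documents give no figure for it. Only g comes from the mismatch.
- **Bias in a known direction.** A reader might infer that early access must make controls resemble treated clients. The Introduction records concerns in Indigenous communities about privacy and technology, so a first contact could lower trust as well as raise it. The documents do not establish the direction.

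**Conclusion.** The point holds as an internal timing conflict. Under the Overview as written, waitlist access opens on or before the due date of the control survey, and the lead equals the unstated interval from baseline to randomisation: 0 days at best, 7 to 14 days for an assumed one to two weeks, about a month on the stated reading of Quantitative Measures. Nothing else in the article corrects it.

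The documents show that exposure before the control survey is possible. They do not show that it occurred, how many clients it reached, or which way it moved scores. For a descriptive pilot this is a moderate fault in the definition of the control measurement. It is worth correcting because the results are meant to inform the design of a later trial, and the schedule could be carried into it.

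**What to change.** **Schedule.** Leave the waitlist access date as stated. Time the 3-month survey from the baseline survey in both arms, with a window (for example the last 7 days) that closes before waitlist access is due. Rewrite the survey timing in Quantitative Measures to the same origin.

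**This cohort.** Results says data collection ran until October 2024, so the timing can no longer be changed. Report each waitlist client's survey and access dates, and flag or show separately any waitlist survey completed after access opened. Carry the corrected schedule into the next trial.

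**Cost.** The text changes are a sentence or so in each of two sections, and nobody's access is delayed. Follow-up is up to about a week short of three months. The immediate arm's exposure at the survey is also shorter by g: with access at randomisation, g = 14 days and a survey 7 days early, it is 91 − 14 − 7 = 70 days. Cost Analysis ties its 3-month horizon to follow-up and counts sessions over 3 months, so it should say whether dose is counted to the survey date or to the full 3 months. A client who answers after the window closes could still have had access first, which is why the dates need recording.

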#### Qualitative Measures

To identify potential service gaps or accessibility concerns in the ShockTalk app, we will conduct in-depth interviews with the practitioners and clients 3 months after treatment participation. Practitioners will be interviewed in a talking circle, a technique consistent with Indigenous methodologies [26]. In the talking circle, practitioners will be asked a series of open-ended questions related to their past experiences with telehealth care linkage systems and how ShockTalk compares with other systems in terms of accessibility, organization, and usability. They will also be asked about their favorite elements of the app, any problems they experienced, and potential improvements that might benefit both the client and the practitioner. The qualitative interview consists of 6 base questions with several probing questions. The talking circle is expected to take 1 to 2 hours.

Clients will also engage in one-on-one in-depth interviews. Although talking circles may be preferable to facilitate discussions, the sensitive nature of the client interviews prevents the study team from conducting discussions of this type. Clients will be asked about their previous experiences in therapeutic contexts, how their experience in therapy resulting from ShockTalk is similar to or different from those experiences, and what could be done to make the app more accessible. Clients are asked to walk through the process of accessing ShockTalk and discuss points at which the app was not intuitive or was problematic. After discussing the process and experience of using the app, clients will be asked about their process in choosing and retaining a therapist—what therapist attributes were most important in deciding on a therapist, what factors influenced a therapeutic fit, and what influenced their likelihood of rescheduling with the therapist they saw. Finally, clients are asked about any potential changes or improvements they would make to improve their experience. Each client interview is expected to take 30 minutes to 1 hour.

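### Client interviews at month 3 across both arms would reach waitlist clients just as access is first offered, and the article also gives a second timing and two interview numbers

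*Protocol article*

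**What the plan says.** **Timing and sample.** Methods, Overview, states: "Qualitative data collection at 3 months from baseline will include 1-hour semistructured interviews". The clients interviewed are a "purposive subsample of 5 clients (selected to reflect a range of engagement and experiences across arms"). The Abstract's Methods paragraph also puts the interviews at 3 months.

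**Access.** Overview allocates clients 1:1 to immediate access or a "3-month waitlist control (5 clients per arm"). It then says: "Waitlist participants will be offered access to the linkage-to-care intervention 3 months after their initial baseline survey is completed".

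**A second timing.** Qualitative Measures plans "in-depth interviews with the practitioners and clients 3 months after treatment participation".

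**Content.** Qualitative Measures says: "Clients are asked to walk through the process of accessing ShockTalk and discuss points at which the app was not intuitive or was problematic". Clients also compare the therapy reached through ShockTalk with earlier therapy and explain how they chose and kept a therapist. They are asked about previous therapy and about improvements too. The full guide is in Multimedia Appendix 1, which is not shown.

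**A second number.** The Objective section of the Introduction describes "interviews with 10 Indigenous mental health treatment seekers in Lenapehoking and 3 practitioners".

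**Enrolment.** Results reports 4 clients enrolled, data collection finished in October 2024 and analysis complete.

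**The concern.** On the Overview schedule, the waitlist arm's access and the interview fall at the same point. A waitlist interviewee would be asked to describe an app not yet used and a therapist not yet found through it. No alternative content for such clients is described.

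The client interviews are the main client-side source on accessibility, experience and value. The two surveys measure help-seeking attitudes and trust, so they do not tell the team where the app was hard to use or how the therapist match worked. Qualitative Analysis keeps separate codebooks for clients and practitioners, but does not separate clients with access from clients without it. Expectations voiced before access could therefore be coded together with accounts of actual use. In a sample of five or fewer, each transcript carries much weight.

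The two timings cannot both be followed for a waitlist client, and the two interview numbers leave the planned sample unclear.

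**Working it through.** There is no power or sample-size figure to reproduce. The check compares timelines and counts interviewees.

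**1. Exposure at interview.** Exposure = interview month − month access is offered.

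| Rule | Immediate-access arm | Waitlist arm |
|---|---|---|
| Access offered (Overview) | month 0 | month 3 |
| Interview under Overview | month 3 | month 3 |
| Exposure under Overview | 3 − 0 = up to 3 months | 3 − 3 = 0 months |
| Interview under Qualitative Measures | 0 + 3 = month 3 or later | 3 + 3 = month 6 or later |

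The last row counts from the earliest possible start of treatment. If the 3 months run from the end of treatment, both entries move later. The two rules can agree for the immediate-access arm. They differ by about 3 months or more for the waitlist arm.

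**2. Content against exposure.** Qualitative Measures summarises six client topics:

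- previous therapy
- therapy through ShockTalk compared with it
- making the app more accessible
- a walk-through of access
- choosing and keeping a therapist
- changes to improve the experience

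Read in context, only the first is clearly answerable without access. The other five presuppose use.

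**3. How many of the 5 could be unexposed.** The article fixes no split, so any figure here is an assumption. Sampling across arms needs at least one client from each arm.

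- Fewest waitlist clients: 1/5 = 20%.
- Most waitlist clients: 4/5 = 80%.
- Balanced split, assumed: 2/5 = 40% or 3/5 = 60%.

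**4. If the Objective's 10 applied at month 3.** All 5 waitlist clients would be included: 5/10 = 50% unexposed.

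**5. Actual enrolment.** With 4 clients, at most 4 interviews are possible, so neither 5 nor 10 was attainable. The arm split of the four is not given. An even split, purely as an assumption, would leave 2 clients in each arm.

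**The case against.** The strongest reply is that Qualitative Measures already gives the sensible rule, because interviews 3 months after treatment participation would let every interviewee speak from use. On that view this is a drafting slip in Overview. Part of that stands: the article does not settle on interviewing waitlist clients before access, and the defect is best described as an unreconciled conflict. But one section does not override the other, and the Abstract is closer to Overview. A team following one section would depart from the other.

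A reader might also infer several stronger things that the documents do not support:

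- *That waitlist clients could not answer the guide at all.* The guide is not shown and may contain branches or probes for clients without access. The previous-therapy question is answerable in any case. The point is limited to the ShockTalk-specific topics.
- *That the sampling phrase contradicts itself because the waitlist arm has no range of engagement.* The range can be read over the whole subsample, so that arm need not contain one of its own.
- *That such interviews would be worthless.* Waitlist clients could speak about randomisation and waiting, which bear on recruitment, retention and acceptability. However, Qualitative Measures lists no such question.
- *That about half of the interviews were in fact uninformative, or that second-hand accounts entered the themes.* The article reports neither who was interviewed, nor when, nor what was coded.

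The interviews are also not the only source for this aim. The practitioner talking circle covers accessibility and usability, and the second survey touches on accessibility. The Objective's 10 may be loose wording for the number of study clients, but as written it differs from 5.

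**Conclusion.** The point holds in a limited form and should be corrected. On the Overview schedule, any waitlist interviewee has essentially zero exposure and cannot speak from experience on most of the described content. Qualitative Measures gives an incompatible timing for that arm, and the Objective and Overview sections disagree on 10 against 5 client interviews.

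The planned number affected is 1 to 4 of 5, or 2 to 3 under an assumed balanced split. The number actually affected among the 4 enrolled clients cannot be derived from the article. The zero-exposure result rests on the Overview timing having been followed and on access not having been given before month 3. The content result rests on the article's summary of the guide.

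**What to change.** **In the text.** Reconcile the Abstract, Objective, Overview and Qualitative Measures on one number of client interviews and one timing. Anchor each interview to that client's own access date, 3 months after access. Select among clients who have had access, including those who booked no session, so that non-use is represented. The cost is a text change and no additional interviews. The small downside is that waitlist interviews fall about 3 months later.

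**For this pilot.** Interviews can no longer be moved. State how many were held and when each took place relative to access, grouped or worded so that none of the four clients can be recognised. Code any interview held before access as expectations and keep it out of the experience and usability themes. This costs a coding flag and a short check of the existing themes.

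**For the future trial.** Carry the access-date anchor into its protocol. If views on waiting or randomisation are wanted from waitlist clients, plan them as a separate topic with its own questions.

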### Study Sample Recruitment

Ten Indigenous clients and 3 Indigenous practitioners will be recruited to assess the feasibility and acceptability of ShockTalk on care linkage among therapists and clients. This proposed sample size aligns with other pilot and feasibility studies, which are not powered for hypothesis testing and are instead based on the pragmatics of recruitment [23]. Therapists will be contacted directly via email from a listserv that was previously compiled through the ShockTalk company website. Therapists who signed up with their names and email addresses and consented to being contacted later will be contacted by our team about their continued interest in ShockTalk and whether they would participate in the pilot program of the app. Indigenous therapy-seeking participants will be recruited via the ShockTalk internal listserv and social media posts on Facebook, Instagram, and X (formerly Twitter), which will include brief information about the study, compensation, and participant expectations.

